### Concealment mechanism {16b}

The unmasked hyperbaric oxygen staff or unmasked study coordinator will only be able to access the randomization form in the database once a participant has been screened and consented, preventing the study team from knowing the next randomization assignment until the participant is randomized.

### Implementation {16c}

Once a patient has been screened and consented, the hyperbaric oxygen staff member will access the randomization assignment in the database.

## Assignment of interventions: blinding

### Who will be blinded {17a}

Masking will be maintained for participants, hospital and gastroenterology research staff, and treating providers. The only unmasked personnel from sites will be the hyperbaric oxygen department/center staff, who require knowledge of the treatment assignment to ensure appropriate interventions are delivered and participants can be monitored and managed appropriately based on the delivered intervention. The DCC includes both masked and unmasked project management staff and statisticians. To prevent accidental contamination, a dedicated unblinded study e-mail account was created for sites to communicate with unblinded DCC team members. Access to randomization assignment and intervention information is restricted to only the unmasked team. Additionally, days 0, 5 and 90 Mayo endoscopic sub-score and Geboes histology score will be done by masked centralized readers.

### Procedure for unblinding if needed {17b}

A participant’s treatment assignment may be unmasked by the unblinded hyperbaric medicine provider if the participant is experiencing symptoms of decompression sickness and knowledge of the treatment assignment is required to treat the adverse event.

## Data collection and management

### Plans for assessment and collection of outcomes {18a}

Demographic information, medical history, ulcerative colitis disease history, and medication use will be collected from the participant and/or medical record. Stool studies to rule out infectious etiologies of presentation will be conducted during screening. A physical examination at baseline and day 90 will assess for any clinical abnormalities and vital signs will be recorded. Daily standard of care blood work will include complete blood count, CRP, erythrocyte sedimentation rate (ESR), and a basic metabolic panel including albumin.

During the 5-day intervention period, data will be collected by the hyperbaric oxygen therapy staff regarding session completion and duration at pressure. Daily intravenous steroids and venous thromboembolism prophylaxis use will be recorded.

An endoscopy with biopsies for histopathology will be conducted at screening, day 5, and day 90. The Mayo endoscopic sub-score and the UCEIS [42] will be ascertained by local treating providers and/or study investigators. Available videos from procedures will be captured for re-review centrally. Stool samples will be collected at screening/baseline, day 5, and day 90. Pre-packaged collection kits with instructions will be provided to sites and utilized to ensure appropriate collection technique for stool.

Clinical assessments will include the Mayo score, Urgency Numeric Rating Scale (NRS), and the simple clinical colitis activity index (SCCAI). The Mayo score is a validated instrument to measure disease activity and is comprised of 4 components: rectal bleeding, stool frequency, physician assessment, and endoscopy appearance [43]. Each component score ranges from 0 to 3, with a total score ranging from 0 to 12 (mild disease activity: 3–5, moderate disease activity: 6–10, severe disease activity: 11–12). The partial Mayo score (excluding the endoscopic measure) will be assessed daily through the active intervention period, with the total score being assessed at screening, day 5, and day 90 to correspond with the timing of endoscopies. The NRS scale is a newly developed, validated, and reliable score designed to assess the severity of bowel urgency [44]. The urgency and nocturnal bowel movement frequency sub-scores of the SCCAI are a validated tool designed to assess colitis exacerbations [45]. The NRS and SCCAI will be collected daily through the active intervention period and at day 90.

Review of changes in medications, new medications or hospitalizations, and adverse event assessments will be conducted throughout the 12-month follow-up. Data from additional endoscopies and intestinal ultrasounds, performed as part of standard of care, within the follow-up period will be collected.

To promote data quality and rigor, site staff will be trained on the protocol and data entry. A data entry vignette will be provided to ensure staff are familiar with entering data into the REDCap project. Additionally, NUDACC will run regular data status and quality reports to identify missing data and potential data entry errors. NUDACC will also perform remote source document verification for one participant per site per year for key data. Data collection forms will be made available upon request.

### Plans to promote participant retention and complete follow-up {18b}

Retention of participants for the study intervention period is anticipated to be 100%, as these participants are hospitalized for their acute flares and are therefore available for daily hyperbaric oxygen therapy sessions. If a participant is discharged prior to day 5, the participant will receive remuneration for returning to complete the daily HBOT sessions. Retention during the 12-month follow-up study period will be optimized by provider contact through routine care given how high risk these participants are for disease relapse and/or progression to biologics or colectomy, and coordinator contact from the local sites. Additional remuneration will be provided for the day 90 standard of care visit and 12-month phone call.

### Data management {19}

NUDACC has designed and built a dedicated REDCap [46, 47] database for the trial. The database mirrors corresponding paper case report forms, and sites have the option of entering data directly into the electronic database or first recording data on paper case report forms. Database access will be audited, and role-based security will be used to provide seamless access and integration to functions such as data entry, data download, and generation of reports. NUDACC will determine and regulate access to data resources through the assignment of security roles, and Data Access Groups will allow for restrictions and control on data entry occurring at each study site.

Centralized training will provide demonstration and ensure comprehension among all relevant study staff at participating sites. Validations for data entry will be programmed wherever possible to ensure consistency and accuracy. NUDACC will also generate a series of data quality assessment scripts as described above. When inconsistencies, discrepancies, or other quality assessment issues are observed, the Data Resolution Workflow module in REDCap will be used to generate queries on specific fields. The Data Resolution Workflow will provide an audit trail for every field for which any discrepancies are noted.

### Confidentiality {27}

Participant privacy and confidentiality will be protected by various security procedures. A study document linking the participant to the study ID will be securely stored at the corresponding clinical center and not transmitted to the DCC. Any paper documents used for data collection will be securely stored within the respective Gastroenterology department of each center for a length of time determined by local site policies. All electronic case report form data will be stored in the secure REDCap database or on secure servers. NUDACC will keep a full copy of the dataset for at least 5 years, and data will be stored indefinitely at the NIDDK Central Repository, as described in {31c}. The site Principal Investigators will ensure confidentiality and masking of study arm.

### Plans for collection, laboratory evaluation, and storage of biological specimens for genetic or molecular analysis in this trial/future use {33}

Pre-packaged collection kits with instructions will be provided to sites and utilized to ensure appropriate collection technique for stool. These will include pre-made bar codes for scanning and storage upon return. All samples will be kept locally in a − 80 °C freezer at each site using de-identified study ID numbers and accession numbers, and batch shipped on dry ice to the central coordination center.

Dedicated research mucosal biopsy specimens will be obtained from participants. We will also rely on the standard of care histopathology specimens being collected during lower endoscopies. Standard of care biopsies at these lower endoscopies will undergo standard pathologic evaluation of colon biopsies and storage of specimens per the Department of Pathology standard protocols at each institution. Additional slides will be created from the standard of care pathology specimens for spatial transcriptomics analyses and centralized histology scoring.

Human biospecimens collected from the trial which remain at the end of the study will be transferred to the central repository. All personal identifiers will be removed from the specimens and the accompanying data prior to transfer. NUDACC will facilitate the transfer of study data, study documentation, study forms, and linkage files (as applicable). All future researchers who utilize those samples must do so under a Usage Agreement which stipulates that researchers will only conduct research consistent with the subjects’ informed consent and will not attempt to identify any individuals.

## Statistical methods

### Statistical methods for primary and secondary outcomes {20a}

Primary analyses will be based on an intention-to-treat principle, whereby all patients will be analyzed as randomized. Descriptive statistics will summarize all baseline variables by arm, and there will be no formal hypothesis testing for comparison of baseline characteristics between treatment arms. Standardized differences in covariates may be examined to evaluate covariate balance across groups. Residual diagnostics will be examined, and relevant assumptions will be assessed using graphical display and statistical testing where appropriate. In situations where modeling assumptions are in question, nonparametric methods, transformations, or inclusion of higher-order terms may be applied.

Primary analyses will employ a logistic regression model to estimate the odds of clinical response in the treatment arm compared to the control arm, adjusting for the stratification factor (bio-naïve or bio-exposed). The odds ratio and 95% confidence interval will be reported with the corresponding p-value.

A linear mixed model will be used for key secondary continuous endpoints (clinical response and CRP), incorporating data from daily assessments (day 2 and day 3). Specifically, the mixed model will include fixed effects for arm (HBOT vs. sham), timepoint (visit day), the interaction between arm at timepoint (to allow for different differences between arms at each visit), corresponding baseline measure, and the stratification factor. For both endpoints, the hypothesis of interest will be based on the difference in score at day 3. For UCEIS (not assessed daily), a linear model will be used to estimate the difference in mean UCEIS score at day 5 between arms adjusting for baseline UCEIS and the stratification factor. In primary analyses, participants with an early colectomy preventing assessment of UCEIS at day 5 will be excluded from the analysis. A correction for multiple testing of the three key secondary endpoints will be incorporated using the Holm method.

Additional secondary analyses will incorporate similar models for all additional binary outcomes. Participants receiving a colectomy prior to the time point of analysis will be considered as ‘non responders’ (e.g., no clinical remission or no endoscopic improvement). A linear mixed model will be used for the continuous endpoint NRS, incorporating data from daily assessments as described above in key secondary analyses. As in primary and key secondary analyses, models will include adjustment for the stratification factor. All additional secondary analyses will be assessed using a two-sided type I error rate of 0.05.

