### Trial design {8}

This two-arm parallel group, multicenter, double-masked trial will randomize 126 participants 1:1 to either HBOT + steroids or sham hyperbaric air + steroids. The study will consist of a 5-day intervention period, followed by a 12-month observational follow-up period, with a standard of care visit at day 90 and a 12-month telephone follow-up. All analyses are based on a superiority framework.

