### Sample size {14}

Sample size estimates were based on the primary aim of detecting a clinically meaningful increase in the frequency of clinical response/remission in the HBOT arm compared to the control arm. Specifically, we estimate that our primary outcome will be achieved in 30% of hyperbaric oxygen treated patients and in 10% of sham hyperbaric air treated patients. Based on combined phase 2 A and 2B trial data, we found 11 of 22 (50%, 95% CI: 28–72%) patients who received the HBOT achieved normalization of rectal bleeding and improvement in stool frequency [28, 29]. Given the small sample sizes of these trials, we have chosen the lower bound of this confidence interval (30%) for the point estimate of the primary outcome in the HBOT arm. Outpatient moderate-severe ulcerative colitis trials have observed a 10% placebo response rate for resolution of rectal bleeding by day 5 of active therapy. Although our population being recruited is sicker and the anticipated placebo/sham response rate would be lower than seen in outpatient trials, we have chosen a conservative estimate of 10% for the primary outcome in sham treated patients. For 80% power, with 1:1 randomization and a 5% two-sided significance level, we estimate we will need 63 patients per arm to detect an absolute difference in clinical remission of 20% (30% in HBOT arm vs. 10% in Sham), based on the standard sample size calculation formula for a two-sample test of proportions.

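### The primary logistic model is valid and adequately powered, but it leaves out baseline severity that is already collected and names no confidence interval for the absolute difference on which the trial was sized

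*Protocol article*

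**What the plan says.** **Primary model.** Protocol article, Statistical methods {20a}: logistic regression for the odds of response in the HBOT arm "compared to the control arm, adjusting for the stratification factor (bio-naïve or bio-exposed"). The between-arm measures named are the odds ratio, its 95% CI and the p-value. Sequence generation {16a} stratifies on that same factor only.

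**Design target.** Sample size {14} puts 63 patients in each group, a number meant "to detect an absolute difference in clinical remission of 20% (30% in HBOT arm vs. 10% in Sham"). It comes from the usual formula for comparing two proportions.

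**Descriptive summary.** Outcomes {12} has the primary outcome summarised as the proportion of responders.

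**Baseline data.** Section {18a}: "Daily standard of care blood work will include complete blood count, CRP, erythrocyte sedimentation rate (ESR), and a basic metabolic panel including albumin". Partial Mayo scores are also taken daily during the intervention, and the full score at screening. In {20a} the mixed models for the symptom score and CRP adjust for the corresponding baseline value, and the UCEIS model adjusts for baseline UCEIS. For the primary outcome, baseline CRP and endoscopic severity appear only in the exploratory subgroup list {20b}.

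**The concern.** Response requires bleeding to reach 0 and stool frequency to fall by at least one point, so starting severity may well predict it. Severity is measured, and the article uses baseline values in its continuous key secondary models, but the primary model does not use them. Section {20a} allows standardised differences between arms to be examined but ties no action to them. If an imbalance in severity appeared, any adjustment of the primary result would be post hoc.

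The second issue is scale. The clinically meaningful effect was set as an absolute difference, while the inferential result is an odds ratio. An odds ratio fixes an absolute difference only once the sham rate is known, and {14} itself expects this sicker population to have a lower sham rate than the outpatient trials behind the 10%. At stake are some precision and a direct answer, with its uncertainty, on the scale used for planning.

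**Working it through.** **1. Reproduce the sample size.** Inputs from {14}: "For 80% power, with 1:1 randomization and a 5% two-sided significance level"; the outcome "achieved in 30% of hyperbaric oxygen treated patients and in 10% of sham hyperbaric air treated patients". Pooled formula with mean rate 0.20:

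n = [1.960·√(2·0.20·0.80) + 0.842·√(0.30·0.70 + 0.10·0.90)]² / 0.20² = (1.109 + 0.461)² / 0.04 ≈ 61.6, so 62 per arm.

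The stated 63 agrees to within one patient. Formula power at 63 is 80.9%.

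**2. Does logistic regression instead of a test of proportions cost power?** Exact unadjusted power at 63 per arm, 30% vs 10%: chi-square 81.7%, likelihood ratio 83.4%, Wald test of the log odds ratio 81.6%. It does not.

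**3. Odds ratio against absolute difference.** Design odds ratio = (0.30/0.70)/(0.10/0.90) = 3.86. Holding it fixed:

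| Sham rate | Implied HBOT rate | Difference |
|---|---|---|
| 5% | 16.9% | 11.9 points |
| 10% | 30.0% | 20.0 points |
| 20% | 49.1% | 29.1 points |

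The same odds ratio covers differences from about 12 to 29 points.

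**4. Chance imbalance.** With 63 per arm, the standardised difference in a continuous covariate has SE √(2/63) ≈ 0.18. An imbalance above 0.2 SD in either direction then has probability 2·[1 − Φ(0.2/0.178)] ≈ 26%.

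**5. Value of one baseline covariate.** The document gives no prognostic strength, so it is assumed. Simulated power, N = 126, marginal rates 30% vs 10%, 3,000 trials per row (Monte Carlo SE of each figure about √(0.82·0.18/3000) = 0.7 points):

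| Covariate OR per SD | Stratum only | Plus covariate |
|---|---|---|
| 1.0 | 81.8% | 81.4% |
| 1.5 | 82.6% | 82.9% |
| 2.0 | 81.0% | 83.4% |
| 2.5 | 82.2% | 85.9% |

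A separate simulation with likelihood-ratio tests, at log-odds per SD of 0, 0.5, 1.0 and 1.5 (OR 1.0, 1.6, 2.7, 4.5), gave 84.3/83.9%, 85.0/86.3%, 84.3/88.1% and 82.2/90.3%. The 8-point gain in its last row needs an odds ratio of about 4.5 per SD and should not be relied on. Under a 10% null, likelihood-ratio rejection was 5.2–5.8% without and 5.6–5.8% with the covariate (2,000 trials each).

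**6. Which covariate.** Table 1 requires bleeding and stool sub-scores of at least 2, and each tops out at 3, so their sum can only be 4, 5 or 6. If the two sub-scores were independent and evenly split (an assumption), the SD would be √(0.25 + 0.25) = 0.71. An odds ratio of 2.0–2.5 per SD would then mean about 7- to 13-fold odds between scores 4 and 6 (2.0 or 2.5 raised to 2/0.71). That is a lot to expect. Eligibility places no limit on CRP.

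**7. Room in the model.** Expected responders: 63·0.30 + 63·0.10 = 18.9 + 6.3 ≈ 25. With arm, stratum and one covariate there are about 25/3 ≈ 8 events per term; with two covariates, about 25/4 ≈ 6.

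**The case against.** The strongest reply is that nothing here is wrong. The model adjusts for exactly the factor used in randomisation. Leaving out other prognostic variables does not bias a randomised comparison or inflate type I error, and the ordinary p-value and interval already allow for chance imbalance. The sample size assumes no covariate gain. Adjusting a continuous outcome for its own baseline is standard practice, so a different covariate set for a binary endpoint, whose stool component is already a change from baseline, is no contradiction. Responder proportions will be reported, so the crude difference can be read off. An analysis plan not shown here may add a risk difference, and more covariates sit uneasily with about 6 expected sham responders.

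Most of this stands, and it rules out three stronger readings. A reader might infer that the primary test is biased or underpowered; steps 1, 2 and 5 show otherwise. A reader might infer that the result cannot be set against the 20-point target at all; the proportions in {12} allow that descriptively. A reader might infer that baseline severity is ignored throughout; it appears in {20b} as exploratory interactions.

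What the reply does not remove is that the article fixes the primary covariate set and the inferential measure. The point is therefore about a stated choice rather than an omitted detail. Crude proportions supply neither an adjusted difference nor a named interval for the effect the trial was built to detect.

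**Conclusion.** The primary analysis is sound and meets its 80% power target. It can be improved at almost no cost in two respects.

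- **Scale.** No confidence interval is named for the absolute difference. This limb rests on the text and simple arithmetic alone: one odds ratio of 3.86 spans about 12 to 29 points as the sham rate goes from 5% to 20%.
- **Precision.** A collected severity measure is left out of the primary model. The gain from adding one is 0 to about 4 power points at assumed odds ratios of 1.0 to 2.5 per SD. It is essentially nil if the covariate is not prognostic, and so is the loss. For the bleeding plus stool score the gain is especially uncertain, because eligibility leaves it only three values.

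This is a recommended refinement, not an error.

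**What to change.** Settle the following before the unblinded sample size re-estimation at about 63 patients, so that the change cannot look data-driven:

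1. Keep the logistic model with arm and the stratification factor.
2. Pre-specify one baseline severity covariate, entered as a continuous term and measured before the first session. Log CRP is preferable. Add the bleeding plus stool score only as a second term, if the number of events allows, under a rule written in advance.
3. Beside the odds ratio, report the standardised (marginal) risk difference from the same model with a 95% CI, and name the interval method (delta method or bootstrap).
4. Compute the interim conditional power from the same model.

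The cost is a few lines of wording, with no change to sample size or data collection. There are two downsides. About 25 expected responders, some 6 of them in the sham arm, restrict the model to one or at most two added terms. The odds ratio also becomes conditional on the covariate and so changes meaning slightly; the standardised risk difference keeps its meaning whichever covariates are used. If the interim has already taken place, add the risk difference as a supplementary estimate and keep the covariate-adjusted model as a sensitivity analysis.

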Key secondary outcomes include (1) clinical response, a continuous measure of the sum of Mayo rectal bleeding and stool frequency sub-scores summarized as the mean at day 3; (2) C-reactive protein (CRP), a continuous measure summarized as the mean at day 3; and (3) endoscopic response, a continuous measure defined by the Ulcerative Colitis Endoscopic Index of Severity (UCEIS) summarized as the mean at day 5. Additional secondary endpoints include (1) steroid-free, colectomy-free, clinical remission (Full Mayo score ≤ 2, with no sub-score > 1), a binary indicator summarized as the proportion at day 90; (2) endoscopic improvement, a binary indicator defined by a Mayo endoscopic sub-score of 0 or 1 summarized as the proportion at day 90; (3) endoscopic remission, a binary indicator defined by a Mayo endoscopic sub-score of 0 summarized as the proportion at day 90; (4) mucosal healing, a binary indicator defined by a Mayo endoscopic sub-score of 0 or 1 and a Geboes histology score ≤ 2 summarized as the proportion at day 90; (5) clinical remission, a binary indicator defined by a full Mayo score ≤ 2 with no sub-score > 1 summarized as the proportion at day 5; (6) need for colectomy, a binary indicator summarized as the proportion at day 90 and (7) the proportion at 12 months; (8) Re-hospitalization for an ulcerative colitis flare, a binary indicator summarized as the proportion at 12 months; (9) Urgency Numeric Rating Scale (NRS), a continuous measure summarized as the mean at day 3; and (10) any serious infection or serious adverse event, a binary indicator summarized as the proportion at day 5. Of note, continuous outcomes violating normality assumptions may be summarized with medians.

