### Methods in analysis to handle protocol non-adherence and any statistical methods to handle missing data {20c}

A sensitivity analysis will be conducted on the per-protocol sample including participants who (1) completed at least 3 full, consecutive intervention sessions, where a “full” session is defined as at least 60 min under pressure; (2) do not have an “early” colectomy, defined as a colectomy on or before day 3; and (3) do not have protocol deviations for unacceptable treatment adjustments through day 3. Results will be used to complement the primary planned analyses based on the intention-to-treat sample.

Given the short time frame and nature of hospitalization, we do not expect any attrition for the primary endpoint. For secondary analyses beyond day 5, we do anticipate larger dropout. In the event of large amounts of missing data (i.e., more than 10%), multiple imputation analyses will be explored. Mechanisms of missing data will be examined, with an assessment of variability in missing rate by participant characteristics. These summarizations will inform potential biases resulting from missing data. If appropriate, multiple imputation methods will be considered in sensitivity analyses. Results will be compared across approaches to assess the effect of missing data, robustness to various model specifications, and validity of specified models.

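### The main day-5 UCEIS analysis drops participants with an early colectomy, although the plan says everyone is analysed as randomised

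*Protocol article*

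**What the plan says.** All references are to the protocol article.

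- **Outcomes {12}** lists as a key secondary outcome "endoscopic response, a continuous measure defined by the Ulcerative Colitis Endoscopic Index of Severity (UCEIS) summarized as the mean at day 5".
- **Statistical methods {20a}**, general rule: "Primary analyses will be based on an intention-to-treat principle, whereby all patients will be analyzed as randomized".
- **Statistical methods {20a}**, UCEIS model: "a linear model will be used to estimate the difference in mean UCEIS score at day 5 between arms", adjusted for baseline UCEIS and the stratification factor. The next sentence says that, in primary analyses, "participants with an early colectomy preventing assessment of UCEIS at day 5 will be excluded from the analysis".
- **Statistical methods {20a}**, multiplicity: "A correction for multiple testing of the three key secondary endpoints will be incorporated using the Holm method".
- **Statistical methods {20a}**, additional binary outcomes: "Participants receiving a colectomy prior to the time point of analysis will be considered as" non-responders.
- **Outcomes {12}**, primary endpoint: response requires that no colectomy was needed, so colectomy counts as failure.
- **Criteria for discontinuing {11b}**: participants withdrawn because of colectomy count as completers, and the colectomy is to be taken into account when endpoints are evaluated, in the way the statistical analysis plan sets out.

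**The concern.** Early colectomy is a failure of treatment that can depend on the assigned arm, and avoiding it is part of the trial's primary objective. Once these participants are removed, the comparison is between those who escaped colectomy in each arm, and randomisation no longer guarantees that the two groups are alike.

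UCEIS is not a minor descriptive endpoint. Its p-value enters the Holm procedure, so it can support a formal claim and it affects the thresholds that the other two key secondary endpoints face. A reader told that the analysis is intention-to-treat would not expect the worst outcomes to be missing from it.

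**Working it through.** **1. The rules side by side**

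| Endpoint | Needs the day-5 endoscopy? | Participant with colectomy before that endoscopy |
|---|---|---|
| Primary clinical response, day 5 | No | Failure |
| Clinical remission (full Mayo score), day 5 | Yes | Non-responder |
| UCEIS, day 5 | Yes | Removed |

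The second and third rows concern the same participant and the same missing endoscopy, handled in two ways. The third row also conflicts with the general intention-to-treat sentence in {20a}, and it is in tension with {11b}.

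**2. What the documents supply for a calculation**

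There is no stated figure for UCEIS to reproduce. The only computable design figure is 63 per arm for the primary endpoint (30% vs 10%, two-sided 5%, 80% power). The pooled two-proportion formula gives 62, and 63 per arm gives 80.9% power, so it reproduces and is not affected here. It serves only to turn rates into patients: 63 × 0.02 = 1.3, 63 × 0.05 = 3.2 and 63 × 0.10 = 6.3 excluded per arm.

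Everything below is assumed, including the scale maximum of 8. Differences are HBOT minus sham, and negative favours HBOT.

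**3. Direction**

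Suppose participants without colectomy have the same mean (5) in both arms. Exclusion then always shows 0. With colectomy scored 8, the difference is (8 − 5) × (HBOT rate − sham rate):

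- 0% HBOT, 5% sham: 3 × (−0.05) = −0.15
- 2% HBOT, 10% sham: 3 × (−0.08) = −0.24
- 5% HBOT, 0% sham: 3 × 0.05 = +0.15

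Exclusion hides benefit in the first two cases and harm in the third.

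**4. Size, by formula**

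Assume normal scores with SD 1.9, a true difference of −1.0, and colectomy in a fraction c of an arm, with correlation ρ between latent UCEIS and the propensity for colectomy. Removing that fraction lowers the arm mean by ρ × SD × k(c), where k(c) = φ(z)/(1 − c) and z is the (1 − c) normal quantile. Values of k are 0.0269 (1%), 0.0494 (2%), 0.0701 (3%), 0.1086 (5%), 0.1616 (8%) and 0.1950 (10%).

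Difference under exclusion = −1.0 + ρ × 1.9 × [k(sham) − k(HBOT)]. For 5% vs 2% with ρ = 1: −1.0 + 1.9 × (0.1086 − 0.0494) = −0.89.

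| Sham vs HBOT colectomy | ρ = 1 (most severe patients) | ρ = 0.5 |
|---|---|---|
| 2% vs 1% | −0.96 | −0.98 |
| 5% vs 2% | −0.89 | −0.94 |
| 8% vs 3% | −0.83 | −0.91 |
| 10% vs 3% | −0.76 | −0.88 |

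In a simulation with ρ = 1, assigning the worst score instead gave about −0.97 to −1.01 for the last three rows. Swapping the rates between arms in those rows turns the ρ = 1 results into −1.11, −1.17 and −1.24.

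**5. Size, by simulation**

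Setting: 63 per arm, 4,000 runs, sham latent mean 5, SD 1.8, latent benefit 0.9, scores rounded and held within 0 to 8, colectomy above a common severity threshold, unadjusted two-sided 5% t-test.

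| Sham (HBOT) colectomy | Exclusion | Worst score | Gap | Power, exclusion vs worst score |
|---|---|---|---|---|
| 2% (0.5%) | −0.83 | −0.87 | 0.04 | 76% vs 79% |
| 5% (1.6%) | −0.77 | −0.87 | 0.10 | 71% vs 79% |
| 10% (3.7%) | −0.70 | −0.89 | 0.19 | 64% vs 78% |

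With no effect and equal colectomy rates there was no bias, and both analyses rejected about 5% of the time. The power figures ignore Holm and baseline adjustment, so only the contrast between the two columns is informative.

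**The case against.** **A participant without a colon has no UCEIS, and the plan states its handling openly.** That is an estimand choice, and {11b} defers details to an analysis plan that is not shown. The phrase about primary analyses also suggests that other handling may appear as sensitivity analyses. This has some force: {11b} gives tension rather than outright contradiction. It does not remove the conflict with the intention-to-treat sentence in {20a}, and an unseen sensitivity analysis would not change the stated main analysis.

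**Few participants may be affected.** Table 1 excludes complications requiring urgent surgery, actual or impending toxic megacolon, and anticipated rescue within 48 hours of randomisation. Medical rescue before day 5 is also allowed. The larger figures above need 5% to 10% colectomy before the day-5 endoscopy, closely tied to UCEIS severity. This stands and limits the size of the problem.

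**Stronger readings that a reader might infer, and that the documents do not support:**

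- *That the plan breaks its own colectomy-as-failure rule.* The non-responder rule in {20a} is written for binary outcomes, and a mean score has no non-responder value. The difference is one of approach.
- *That exclusion would flatter HBOT if HBOT merely delayed surgery.* Delay means fewer HBOT colectomies before day 5, so severe patients stay in the HBOT mean and count against it.
- *That the per-protocol set has the same fault*, because it removes early colectomy, "defined as a colectomy on or before day 3". That set is labelled a sensitivity analysis. It also requires three full consecutive sessions, which with daily sessions already rules out a participant with colectomy on day 1 or 2.

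**Conclusion.** The point holds as a should-fix. The main UCEIS analysis is not the intention-to-treat analysis that the same section announces, and it handles colectomy differently from the primary endpoint and the binary secondary endpoints.

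The direction depends on the colectomy rates before day 5. In the direction the trial hopes for (fewer colectomies on HBOT), the bias is towards no effect and costs power. It favours HBOT only if HBOT raises early colectomy.

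For a true difference of about −0.9 to −1.0, the distortion is about 0.04 points or less when sham colectomy is about 2%. It rises to about 0.2 points at 10% if colectomy occurs in the most severe patients, and to about half that if severity and colectomy are only moderately correlated (ρ = 0.5). The colectomy rates, SD, UCEIS effect and scale maximum are all assumptions.

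The concern does not reach the primary endpoint, and need for colectomy is reported separately at day 90 and 12 months. That is why it does not rank higher.

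**What to change.** In {20a}, and in the analysis plan to match, replace the exclusion with a rule that keeps every randomised participant in the main UCEIS analysis. Those with colectomy before the day-5 endoscopy receive the worst possible score in the planned linear model, or the worst rank in a rank-based ANCOVA with baseline UCEIS and the stratification factor. Name one of the two as the main analysis before any unblinded look at the data. Report the version without these participants as a sensitivity analysis, with the number excluded in each arm.

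If the team prefers to keep the exclusion as the main analysis, the least that is needed is to state that it describes participants without early colectomy and to stop calling it intention-to-treat.

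The cost is wording only: no extra data, visits or sample size. The small downside is that the estimate becomes a composite of endoscopic severity and colectomy and must be described that way.
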